#### 4.2 Pre-trial screening and re-screening (day -28 to day -2)

Patients will be eligible for screening provided that:

- They give separate written informed consent for completing the self-rating mood questionnaires.
- The Investigator anticipates that there is a reasonable expectation that they will satisfy the remaining inclusion criteria see section 4.1 above (NB formal screening for the main study should not be performed until the outcome of the mood questionnaires of the patient is known).

To obtain a screening number, complete a Screening Form and fax/email it to the BKM120 Trial Office.

Patients who do not meet the inclusion/exclusion criteria first time round will not be re-screened.

#### 4.3 Patient registration procedure

Potential participants will have been referred to oncology services for management of NSCLC and be considered suitable for palliative radiotherapy treatment by their multidisciplinary team. The study team will maintain screening

and study enrolment logs for all patients approached concerning the study. The log will include details of patients subsequently excluded along with the reason for the exclusion.

Protocol waivers to deviate from the entry criteria will not be granted.

A patient registration/eligibility check-list must be completed and passed to the BKM120 Trial Office.

Before entering a patient onto the study the Principal Investigator or designee will confirm eligibility. If in any doubt the Chief Investigator must be consulted before entering the patient. Details of the query and outcome of the decision must be documented on the registration/eligibility checklist.

After completing suitability checks, the Informed Consent Form for trial participation and the Registration Form for the patient, site staff will email/fax the Registration Form to the BKM120 Trial Office to confirm the patient's eligibility. The patient will then be registered, where applicable, to one of the cohorts.

Once the investigator / research nurse has a study number for the patient, they will be asked to provide the original Registration Form and a copy of the patient's histology report (which will identify the patient by study number only) to the Trials office. This will allow the Trial Office to confirm the disease stage of patients entering the study.

## 5 TRIAL ASSESSMENTS AND PROCEDURES

Please refer to the Schedule of Events given at the front of this protocol. Details of all protocol evaluations and investigations must be recorded in the patient's medical record for extraction onto the CRF.

### 5.1 Informed consent for screening and main study

Informed consent will be a two stage process. Firstly potential participants will be asked to provide consent for screening. If the potential patients are successfully screened they will be asked to consent to the main study.

Potential participants will be given a current, approved version of the patient information sheet. They will also receive clear verbal information about the study detailing no less than: the nature of the study; the implications and constraints of the protocol; the known side effects and any risks involved in taking part. It will be explained that they will be free to withdraw from the study at any time, for any reason, without prejudice to future care, and with no obligation to give a reason for withdrawal.

They will have at least 24 hours to consider the information provided and the opportunity to question the Investigator, their GP or other independent parties before deciding whether to participate. The Investigator or designee who obtains consent must be suitably qualified and experienced, and be authorised to do so by the Chief/Principal Investigator. The Investigator is responsible for ensuring that the trial consent procedures comply with current applicable GCP Regulatory and ethical requirements. Informed consent discussions and outcomes must be well documented in the medical record. The Investigator or designee must be satisfied that the patient has made an informed decision before taking consent. The patient and the Investigator or designee must personally sign and date the current approved version of the informed consent form in each other's presence. A copy of the information and signed consent form will be given to the participant. The original signed form will be retained at the study site. A copy must be held in the Investigator Site File if retaining the original in the medical record.

#### ***Contraceptive/ Pregnancy counselling***

All participants must be advised on the need to use reliable methods of contraception during the study. The advice should include:

- (1) The acceptable methods, including: male or female sterilization, some intrauterine devices (IUDs), and abstinence.
- (2) The recommendation that a barrier method should be used in addition to another form of contraception.
- (3) Males should continue to take these precautions for a minimum of 16 weeks after the last dose of study drug. Female partners of men enrolled in the study should continue to use acceptable methods of contraception for 16 weeks after the final dose of BKM120.
- (4) Female patients in the study should continue to take these precautions for a minimum of 4 weeks after the last dose of study drug.

- (5) That any pregnancy that occurs during administration of the study drug will be followed up and the outcome of all pregnancies (spontaneous miscarriage, elective termination, normal birth or congenital abnormality) will be reported and followed up even if the participant is discontinued from the study.

#### Evaluations at screening (day -28 to day -2) for all cohorts

- Written informed consent for Screening.
- Patient self-rating mood scales for depression (PHQ-9) and anxiety (GAD-7).

#### 5.2 Pre-dosing evaluations for all cohorts

The following must be performed/obtained within 4 weeks before the patient receives the first study dose.

- Written informed consent for Main Study.
- Demographic details.
- Medical History including prior diagnosis, prior treatment and concomitant diseases.
- Concomitant medications.
- ECOG performance status.
- Patient self-rating mood scales for depression (PHQ-9) and anxiety (GAD-7).
- Haematology – Hb, white blood cells (WBC) with differential count (neutrophils and lymphocytes), platelets and INR.
- Biochemistry – sodium, potassium, calcium, magnesium, phosphate, urea, creatinine, albumin, bilirubin, alkaline phosphatase (alk phos), AST, ALT, LDH, HbA1c and lipase.
- Fasting plasma glucose (FPG)  $\leq 120\text{mg/dL}$  [6.7 mmol/L].
- Research blood sample for PBMC pAkt level.
- Urinalysis (Blood, White Cells, Protein and Nitrites) &/or dipstick for proteinuria.
- Electrocardiogram (ECG).
- Histological confirmation of NSCLC.

#### 5.3 Evaluations during the study for cohorts 1-3 plus the expansion cohort

An illustration of the schedule for patients in cohorts 1-3 is shown below. Treatment with BKM120 starts on Day 1 and continues until day 14. Radiotherapy treatment starts on day 8 and continues until day 14.

The MTD will be determined as described in Section 8.1. An additional expansion cohort of a further six patients will be treated with BKM120 in combination with radiotherapy at whichever cohort (1-3) corresponds to the MTD.

[figure not shown]

The breakdown of the investigations performed at each visit for patients in cohorts 1-3 are summarised below:

### Evaluations on day -1

On the day **before** the first dose of BKM120 is given:

- Physical examination including height and weight.
- ECOG performance status.
- Patient self-rating mood scales for depression (PHQ-9) and anxiety (GAD-7).
- Vital signs: systolic / diastolic blood pressure (BP), pulse rate.
- Evaluation of toxicity (NCI CTCAE v 4.0).
- Patients will undergo F-Miso PET-CT and perfusion CT scans.
- Blood samples from F-Miso PET-CT.
- Pregnancy test: serum or urine Human Chorionic Gonadotropin (HCG) test to rule out pregnancy at study entry; results must be obtained and reviewed before the first dose of BKM120 is administered.
- Patients will be supplied with BKM120 and will commence treatment on day 1.

### Evaluations on day 8

- Haematology – Hb, white blood cells (WBC) with differential count (neutrophils and lymphocytes), platelets and INR.
- Biochemistry – sodium, potassium, calcium, magnesium, phosphate, urea, creatinine, albumin, bilirubin, alkaline phosphatase (alk phos), AST, ALT and LDH.
- FPG.
- Research blood sample for PBMC pAkt level.
- Physical examination including weight.
- Concomitant medications.
- ECOG performance status.
- Patient self-rating mood scales for depression (PHQ-9) and anxiety (GAD-7).
- Vital signs: systolic / diastolic blood pressure (BP), pulse rate.
- Evaluation of toxicity (NCI CTCAE v 4.0).
- Patients will undergo F-Miso PET-CT and perfusion CT scans.
- Blood samples from F-Miso PET-CT.
- Patients will commence radiotherapy treatment after the imaging investigations have been completed.

### Evaluations on day 14

- Haematology – Hb, white blood cells (WBC) with differential count (neutrophils and lymphocytes), platelets and INR.
- Biochemistry – sodium, potassium, calcium, magnesium, phosphate, urea, creatinine, albumin, bilirubin, alkaline phosphatase (alk phos), AST, ALT, LDH and lipase.
- FPG.
- Urinalysis (Blood, White Cells, Protein and Nitrites) &/or dipstick for proteinuria.
- Electrocardiogram (ECG).
- Research blood sample for PBMC pAkt level.
- Physical examination including weight.
- Concomitant medications.
- ECOG performance status.
- Patient self-rating mood scales for depression (PHQ-9) and anxiety (GAD-7).
- Vital signs: systolic / diastolic blood pressure (BP), pulse rate.
- Evaluation of toxicity (NCI CTCAE v 4.0).
- Patients will complete both radiotherapy and BKM120.

### Evaluations on day 28

Two weeks after completion of treatment, patients will undergo:

- Haematology – Hb, white blood cells (WBC) with differential count (neutrophils and lymphocytes), platelets and INR.
- Biochemistry – sodium, potassium, calcium, magnesium, phosphate, urea, creatinine, albumin, bilirubin, alkaline phosphatase (alk phos), AST, ALT and LDH.
- FPG.

- Research blood sample for PBMC pAkt level.
- Physical examination including weight.
- Concomitant medications.
- ECOG performance status.
- Patient self-rating mood scales for depression (PHQ-9) and anxiety (GAD-7).
- Vital signs: systolic / diastolic blood pressure (BP), pulse rate.
- Evaluation of toxicity (NCI CTCAE v 4.0).

#### Evaluations on day 56

Six weeks after completion of treatment, patients will undergo:

- Haematology – Hb, white blood cells (WBC) with differential count (neutrophils and lymphocytes), platelets and INR.
- Biochemistry – sodium, potassium, calcium, magnesium, phosphate, urea, creatinine, albumin, bilirubin, alkaline phosphatase (alk phos), AST, ALT, LDH and lipase.
- FPG.
- Urinalysis (Blood, White Cells, Protein and Nitrites) &/or dipstick for proteinuria.
- Electrocardiogram (ECG).
- Research blood sample for PBMC pAkt level.
- Physical examination including weight.
- Concomitant medications.
- ECOG performance status.
- Patient self-rating mood scales for depression (PHQ-9) and anxiety (GAD-7).
- Vital signs: systolic / diastolic blood pressure (BP), pulse rate.
- Evaluation of toxicity (NCI CTCAE v 4.0).

A dose escalation decision will be made after the last patient in each cohort has completed day 56 evaluation. The dose escalation will be based on the prevalence of dose limiting toxicities as defined in Section 8.1.

#### 5.4 Evaluations during the study for cohort 4

An illustration of the schedule for patients in cohorts 4 is shown below. Treatment with BKM120 starts on Day 1 and continues until day 28. Radiotherapy treatment starts on day 22 and continues until day 28.

[figure not shown]

The breakdown of the investigations performed at each visit for patients in cohort 4 are summarised below:

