| Blood test for pAkt measurement                                            | X                |        |                         | X                    | X      | X      | X      |
| Coagulation (INR)                                                          | X                |        |                         | X                    | X      | X      | X      |
| Urinalysis                                                                 | X                |        |                         |                      | X      |        | X      |
| Dispensing of BKM120                                                       |                  | X      |                         |                      |        |        |        |
| BKM120 a                                                        |                  |        | Once daily              |                      |        |        |        |
| Radiotherapy                                                               |                  |        |                         | 20 Gy in 5 fractions |        |        |        |
| Pregnancy test (if applicable)                                             |                  | X      | If clinically indicated |                      |        |        |        |

aBKM120 taken at 50mg, 80mg, 100mg (cohorts 1-3 respectively) or MTD (expansion cohort) once daily continuously on days 1-14

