### Clinical

BKM120 has previously been used in a single-agent phase I study (summarised in the table below). It is currently being used in clinical trials in combination with both chemotherapies (e.g. paclitaxel and carboplatin) and biological therapies (trastuzumab). There are currently no trials combining BKM120 with radiotherapy treatment.

Potential risks to participants include the following:

- Exposure to an investigational agent with corresponding side effects. In addition to the main toxicities associated with this treatment (see table below) it is possible that BKM120 may increase the side-effects associated with radiotherapy.
- Adding BKM120 to radiotherapy may not be as effective as standard radiotherapy alone. This risk is very small as there is no laboratory evidence to suggest this might happen.
- Exposure to ionising radiation from the additional research scans. However, this dose is minimal in comparison with the radiotherapy dose. Additionally, the patients in this study have a limited life expectancy due to their advanced cancer and are therefore unlikely to be harmed by the long-term effects of radiation

exposure. These scans are purely for research purposes and clinical management is unlikely to be altered as a result of this imaging.

- Discomfort and bruising due to the additional research blood tests.

Potential benefits to participants include:

- Access to a novel drug which is not available outside of a clinical trial. BKM120 has shown evidence of clinical activity when used as a single-agent. However, it is not clear whether such responses are likely when the drug is used for shorter periods, as in this trial.
- BKM120 may increase the efficacy of radiotherapy. This may result in improved local disease control, with a greater improvement in patient's symptoms.

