  - Surgical sterilization: Have had bilateral oophorectomy (with or without hysterectomy) or tubal ligation at least six weeks before taking BKM120. In case of oophorectomy alone, only when the reproductive status of the woman has been confirmed by follow up hormone level assessment.
  - Male partner sterilization (with the appropriate post-vasectomy documentation of the absence of sperm in the ejaculate). [For female study patients, the vasectomised male partner should be the sole partner for that patient]
  - Or use of a combination of any two of the following (a+b):
    - a) Placement of an intrauterine device (IUD) or intrauterine system (IUS)
    - b) Barrier methods of contraception: condom or occlusive cap (diaphragm or cervical/vault caps) with spermicidal foam/gel/film/cream/vaginal suppository

Female patients must use acceptable methods of contraception must continue to use contraception for at least 4 weeks after completing BKM120. Male patients (and their female partners) will need to continue to use contraception for at least 16 weeks after completing BKM120.

**Women of child-bearing potential must have a negative serum pregnancy test  $\leq$  72 hours prior to initiating treatment**

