### 12.1 Tumour assessment

Response to BKM120 treatment will be based upon changes in tumour hypoxia and perfusion as detected by  $^{18}\text{F}$ -Miso PET-CT scans and perfusion CT scans respectively. These imaging investigations will be performed the day prior to commencing BKM120 treatment, and on the day that radiotherapy treatment commences. The imaging investigations will be repeated prior to the patient receiving their first fraction of radiotherapy.

The rationale for this timing is to observe whether BKM120 can reduce tumour hypoxia and increase tumour perfusion, since both of these changes would be likely to increase the efficacy of radiotherapy treatment.

Establishing the appropriate method for analysis of both imaging techniques is part of the research question. Once established the same method of assessment and the same technique will be used throughout the trial. Changes in tumour-to-blood ratio (TBR) mean and volume will be identified with  $^{18}\text{F}$ -Miso PET-CT imaging and changes in tumour blood flow, blood volume, and mean transit time assessed with perfusion CT imaging.

If there is no change in tumour hypoxia or perfusion following one week of BKM120 treatment, patients will be recruited to cohort 4 where they will receive three weeks of BKM120 at the MTD prior to commencing radiotherapy.

Perfusion CT and dynamic  $^{18}\text{F}$ -Misonidazole PET-CT scans will be performed as summarised in Sections 5.3 and 5.4. Each patient will be classified as a 'responder' or 'non-responder' on the basis of their pre- and post- BKM120 imaging. Those patients whose imaging demonstrates the presence of a physiological response on either perfusion CT and/or  $^{18}\text{F}$ -Misonidazole PET-CT will be classified as a responder whilst those that do not show a response on either imaging modality will be classed as a non-responder.

Patients will only be recruited to cohort 4 if more than 50% of the patients treated with the MTD of BKM120 ( $n = 9$  to 12 evaluable) are defined as non-responders. The following is considered guidance and the statistical analysis of the imaging endpoints will be detailed in the SAP with approval from the DSMC/TSC.

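### The pregnancy result is due only before the first BKM120 dose, so the day -1 research scans may be done before it is known

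*Protocol*

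**What the plan says.** The protocol deals with the pregnancy test in four places and with the baseline scans in three.

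- **Day -1 lists, sections 5.3 and 5.4.** A serum or urine test is done on the day before dosing. Its purpose is given as a "test to rule out pregnancy at study entry", and its deadline as "results must be obtained and reviewed before the first dose of BKM120 is administered". The wording is the same for cohorts 1-3, the expansion cohort and cohort 4.
- **Exclusion criterion 21, section 4.1 and synopsis.** Pregnant women are excluded. "Women of child-bearing potential must have a negative serum pregnancy test", and the window is no more than "72 hours prior to initiating treatment".
- **Both schedules of events.** The pregnancy test is marked on day -1, with nothing in the day -28 to day -2 column. After day -1 it is repeated only if clinically indicated.
- **Screening list in section 5.1 and pre-dosing list in section 5.2.** Neither contains a pregnancy test.
- **Baseline scans.** The day -1 lists include "F-Miso PET-CT and perfusion CT scans". Section 12.1 confirms the timing: "These imaging investigations will be performed the day prior to commencing BKM120 treatment, and on the day that radiotherapy treatment commences". Section 12 says that imaging follows a departmental protocol.
- **Risk statement, section 1.4.** "Exposure to ionising radiation from the additional research scans" is listed among the risks to participants, and the scans are described as serving research alone.

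**The concern.** The two halves of the day -1 sentence fit poorly together. The stated purpose reaches back to study entry, but the deadline reaches only to the first capsule. The baseline FMISO PET-CT and perfusion CT fall between the two. They are the first trial procedures with a radiation exposure, and they have no clinical purpose for the patient.

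A woman who is pregnant without knowing it could therefore be given a radiotracer, a PET-CT and a contrast CT for research before a result shows that she is ineligible. Section 1.4 plays down the radiation risk on two grounds: the scan dose is small beside the radiotherapy dose, and the patients' life expectancy is limited. Neither ground applies to a fetus, and a woman found pregnant at this point would not go on to trial treatment. A minor further cost is a baseline scan pair spent on a patient who cannot be dosed.

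**Working it through.** No formula applies. The check is whether any statement in the protocol makes a pregnancy result precede the day -1 scans.

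| Time | Scheduled | Is a pregnancy result required by then? |
|---|---|---|
| Day -28 to day -2 | Eligibility criteria checked, bloods, ECG, mood scales | No test listed (screening list in 5.1, list in 5.2, both schedules) |
| Day -1 | Pregnancy test, FMISO PET-CT, perfusion CT, dispensing of BKM120 | Test done; no order set between the result and the scans |
| Day 1 | First BKM120 dose | Yes: result obtained and reviewed |

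1. **Deadline.** Sections 5.3 and 5.4 name one event that must wait for the result, which is the first dose. The scans are not named.
2. **Eligibility rule.** Criterion 21 counts its window back from the start of treatment. It permits a test before the scans but does not require one.
3. **Eligibility confirmation.** Section 4.3 requires eligibility to be confirmed before entry and allows no waivers. The only scheduled test, however, falls on day -1, after the screening column has closed. Confirmation during screening therefore cannot rest on a scheduled pregnancy result.
4. **Order where the protocol wants one.** On day 8 (cohorts 1-3 and expansion cohort) and day 22 (cohort 4), radiotherapy is expressly held until imaging is complete. No similar statement links the pregnancy result to imaging on day -1.
5. **Result.** Scanning on day -1 and reviewing the result later that day, or on day 1 before the dose, meets every requirement in the text. Testing first meets them equally.
6. **Room to move the deadline.** Section 8.2 has BKM120 taken in the morning from day 1. If the scans start on the morning of day -1, that is about 24 hours before the dose, so about 72 - 24 = 48 hours of the existing window lie before the scans. A result can be obtained in that time without widening the window.

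One contradiction appears at the same place. Criterion 21 requires a serum test, whereas the day -1 lists accept serum or urine. A woman with a negative urine test on day -1 meets the visit list but not the eligibility criterion.

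**The case against.** The strongest reply is that the protocol states a wider purpose than protection from the drug. A test to exclude pregnancy at entry can be read as preceding any study procedure. This part stands: it would be wrong to infer that the check is aimed only at BKM120. It does not settle the matter, because the same sentence then sets the first dose as the deadline.

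A reader might also infer that sites are told to scan first, because the scans stand above the pregnancy test in the day -1 lists. The documents do not support that. The lists are unordered bullets, and the protocol says so expressly when it wants a sequence. The defect is silence on order, not a wrong instruction.

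A third inference is that nothing at all holds the scans until the result is known. That is established only for this protocol's own text. Imaging follows a departmental protocol that may well include a pregnancy check. Its content is not shown, and this protocol does not say that it covers pregnancy, so it can be neither relied on nor dismissed.

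Other safeguards lower the likelihood. Women of child-bearing potential must use the specified contraception, eligibility is confirmed before entry, and waivers are not granted. None of these is a test result tied to the scan.

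Finally, the study is small, with 2-30 evaluable patients planned at one centre. The primary endpoint, the DLT rules and the escalation decisions are untouched. This is a fair limit on the weight of the point.

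**Conclusion.** The point holds as a gap in ordering. The pregnancy result is required before the first dose but not before the research scans of the previous day, no earlier test is scheduled, and scanning before the result is known is compliant.

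The gap is of low frequency. The protocol gives no number of women of child-bearing potential. That few will be enrolled is a judgement about this population, not a figure from the document, and the conclusion does not depend on it. No endpoint, analysis or dose decision is affected. The case for a change is that the exposure is avoidable, has no clinical benefit to the patient, and can be prevented within a window that the protocol already allows.

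The conclusion rests on the protocol text alone. If the departmental imaging protocol already requires a negative result before FMISO PET-CT and perfusion CT, practice is safe and only the wording needs to catch up.

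**What to change.** - In the day -1 lists of sections 5.3 and 5.4 and in both schedules of events, require the pregnancy result to be obtained and reviewed before the day -1 research scans as well as before the first BKM120 dose. State that the sample may be taken before day -1, within the existing 72-hour window.
- In the same edit, reconcile the serum test in criterion 21 (section 4.1 and synopsis) with the serum or urine test in the day -1 lists, so that one result serves both eligibility and the visit.

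The change takes one sentence in each of the two sections and a footnote to each schedule. No extra test is needed. For the few women concerned it means either a short wait on day -1 before an FMISO session whose last scan comes about 4 hours after injection, or a slightly earlier blood sample, which might need a separate attendance.
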